### Treatment plan and modifications

The study treatment commences on the day prior to the scheduled AVF surgery and will continue for 3 months. Participants will take 100 mg of Aspirin per day p.o. or matching placebo and 4 g of omega-3 fatty acids in divided doses (2 g twice daily) in the form of Omacor capsules, 45% eicosapentaenoic acid (EPA) and 45% docosapentaenoic acid (DHA), or matching placebo.

Compliance will be monitored by capsule/tablet count at scheduled study visits at week 1, 6 and 12. Selected centres will also measure erythrocyte fatty acids for compliance with omega-3 fatty acid intake and urinary thromboxane B2 levels (for patients with urine output) for compliance with aspirin intake. Centres will apply routine biochemistry (lipids, CRP) and haematology analyses as part of patient monitoring.

Study treatment may be discontinued if one of the following occurs:

1. A major bleeding event (e.g. haemorrhagic stroke, gastro-intestinal bleed);

2. The access is abandoned due to thrombosis at any time after the one week assessment;

3. An AVG rather than an AVF is created, or a vein graft is used;

4. Anti platelet therapy or anticoagulation is indicated because of other co morbid events i.e. for example a major cardiovascular event;

5. A female patient becomes pregnant while on study medication. The event should be reported to the trial coordinating centre immediately as a medically important SAE. The event will be reported to Bayer Safety within 24 hours by the coordinating centre and follow up performed through to delivery;

6. The AV anastomosis is created in the lower limbs rather the upper limbs during surgery.

7. Patient receives renal transplant

Study treatment should be continued if:

1. Further access is created (including a new AVF or AVG, peritoneal and venous catheter) because of failure of maturation of the study AVF, i.e. access is still patent;

2. Renal function is recovered; the study AVF can still be measured for patency.

No other anti-platelet or anti-coagulation agent will be permitted during the period the patient is taking study medication.

### Statistical Considerations

#### Sample size calculation for the primary outcome

The event rate for the primary outcome (failure of primary patency) is estimated to be 25% at three months in the control group. If a 30% relative risk reduction is achievable with either aspirin or omega-3 fatty acids, then with 80% power and a significance level of 5%, 1200 study subjects will be required (300 receiving double placebo, 300 active aspirin and placebo omega-3 fatty acids, 300 active omega-3 fatty acids and placebo aspirin, and 300 both active aspirin and active omega-3 fatty acids in a factorial design). This allows for 5% drop-in from placebo to active treatment (either aspirin or omega-3 fatty acids), 5% drop-out from study treatment (to no treatment – assumed equivalent to placebo), and 5% loss to follow-up. This is equivalent to an observed relative risk reduction of 24%. Without adjustment for compliance, the study size needed would have been 932 subjects.

The study is not adequately powered to detect a clinically important difference between the combination of aspirin and omega-3 fatty acids and either treatment alone, but preliminary data on the combination will be obtained. The event rate of the primary outcome, primary failure, is based on review of all papers published in this area. The effect size, a 30% reduction, is based on the smallest size of the effect the proposing clinicians believe would lead to a change in practice (incorporation of intervention) should the trial prove the intervention is efficacious.

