#### Sample size calculation for the secondary outcome

Sample size is estimated for the secondary outcome (failure of patency at 6 months) under assumptions of additive or multiplicative effects for each of 3 placebo rates. The calculation below is based on the following assumptions: 5% loss to follow up, 15% drop-in and 5% drop-out. The baseline failure rate of patency at 6 months is (40%, 50% and 60%) in the placebo group, the use of either aspirin or omega-3 fatty acids alone results in a relative risk reduction (RRR) of 25%, i.e. the failure rate becomes respectively 30%, 37.5% and 45% for a patient taking only one drug.

The sample size calculation is based on a marginal analysis (Z-test) with two-sided α = 0.05, power β = 90%. Table 2 presents required sample sizes under additive model (bold) and under multiplicative model

**Table 2 T2:** The sample sizes required under the additive and multiplicative models for the secondary outcome – functional patency

	Total sample size			
	
	Additive model		Multiplicative model	
	
Patency failure rate at 6 months for placebo group	unadjusted	adjusted	unadjusted	adjusted
40%	**874**	**1455**	1156	1812
50%	**620**	**1034**	820	1297
60%	**452**	**752**	596	941

(Unadjusted and adjusted refer to the calculations of sample size without and with adjustment for loss to follow-up (5%), drop-in (15%) and drop-out (5%))

A recently published comparable trial in the United States [16] experienced a placebo rate of 60% for failure of patency at 6 months. We are confident that a sample size based on a placebo rate of at least 50% is a realistic estimate and that the sample of 1,200 recruited for the primary outcome will generally be adequate for the secondary outcome whether the effect is additive or multiplicative.

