### Analysis

Analysis of the primary outcome (patency) will be on an intent-to-treat basis. All randomised patients will be analysed in the group they were allocated to, even if they do not receive treatment as allocated, or do not commence treatment. All randomised patients will be included in the analysis.

The primary outcome is measured as the proportion with failure of patency at three months after randomisation. The primary hypothesis will be tested using a chi-square test of proportions to test the null hypotheses that a) the proportion of failures in those allocated to aspirin versus those allocated to placebo aspirin is equal, and b) the proportion of failures in those allocated to omega-3 fatty acids versus those allocated to placebo omega-3 fatty acids is equal. The primary outcome will be measured at 84 days after randomisation, with a permitted tolerance of 7 days prior, and 14 days after the due date of 84 days. Tests of hypotheses will be at the 5% significance level, and 2-sided p-values will be used.

Any patient who does not have a 84-day measure will be counted as failure of patency in the primary analysis. A secondary analysis will be done including only those with a 84-day measure to test the sensitivity of the analysis of the main treatment comparisons to patient exclusions. As this is a short-term intervention, with a relatively short recruitment period, the only planned interim analysis is of safety. This will be conducted at 1/3 and 2/3 of total patient numbers accrued. Similar analyses to the primary one will be undertaken on the secondary outcomes, as well as exploratory analyses looking at the validity of the chosen primary outcome and its correlation with other outcomes, and the prediction of thrombosis from baseline variables such as markers of inflammation.

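### The stated 24% observed relative risk reduction does not follow from 5% drop-in and 5% drop-out, which give about 27%; the 1,200 patients agree with 27%

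*Protocol article*

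**What the plan says.** The protocol article, under Sample size calculation for the primary outcome, starts from this control rate: "The event rate for the primary outcome (failure of primary patency) is estimated to be 25% at three months in the control group". The effect is conditional: "If a 30% relative risk reduction is achievable with either aspirin or omega-3 fatty acids". The size follows: "with 80% power and a significance level of 5%, 1200 study subjects will be required", in four groups of 300, so that each main effect compares 600 with 600.

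On non-compliance it states: "This allows for 5% drop-in from placebo to active treatment (either aspirin or omega-3 fatty acids), 5% drop-out from study treatment". Patients who drop out are taken to behave as on placebo, and 5% loss to follow-up is added. The diluted effect is then summarised: "This is equivalent to an observed relative risk reduction of 24" per cent. Without adjustment for compliance the article gives 932 subjects.

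The Analysis section fixes the test ("The primary hypothesis will be tested using a chi-square test of proportions", for each drug against its placebo) and its level ("Tests of hypotheses will be at the 5% significance level, and 2-sided p-values will be used"). It also counts any patient without an 84-day measure as a failure in the primary analysis.

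**The concern.** Crossover of 5% in each direction shrinks a risk difference by a factor of about 0.90, so a 30% reduction should become about 27%, not 24%. Loss to follow-up, if it only removes patients, changes the number evaluable and leaves the ratio alone. The sentence giving 24% therefore seems not to belong with the sentences around it.

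The diluted effect is what an intention-to-treat analysis estimates, so readers will use it as the benchmark when they interpret the result, above all a null one. As printed, the article claims 80% power for an observed 24% reduction, which the trial would have only about 70% power to detect.

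**Working it through.** **Inputs** (protocol article, primary sample size and Analysis sections): control 25%; relative reduction 30%, so active 17.5%; two-sided 5%; power 80%; two equal sides per main effect; drop-in 5%; drop-out 5%; loss 5%.

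**Formula.** For rates c and t with mean p, the number per side is

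n = [1.960·√(2p(1−p)) + 0.842·√(c(1−c) + t(1−t))]² / (c−t)²

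This is the pooled-variance form without continuity correction. Power with m per side is Φ{[(c−t)√m − 1.960·√(2p(1−p))] / √(c(1−c) + t(1−t))}.

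**1. The article's unadjusted figure.** For 0.25 versus 0.175: (1.960×0.5785 + 0.842×0.5761)² / 0.075² = 2.620/0.005625 = 465.8, rounded up to 466 per side, 932 in total. This matches the printed figure exactly, so the formula is very likely the sponsor's.

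**2. Dilution by the stated crossover.**
- Control: 0.95×25% + 0.05×17.5% = 24.625%
- Active: 0.95×17.5% + 0.05×25% = 17.875%
- Difference: 6.75 points
- Relative reduction: 1 − 17.875/24.625 = 27.4%, or 6.75/25 = 27.0% if the undiluted control rate is the base

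**3. Sample size at the diluted rates.** n = 2.6215/0.0675² = 575.4 per side, 1,151 in total (1,152 if each side is rounded up). Dividing by 0.95 for loss gives 1,211 (1,213), against a printed 1,200. Power is 81.6% with 1,200 evaluable and 79.6% with 1,140 (1,200×0.95).

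**4. Sample size and power at an observed 24%.** For 25% versus 19%, n = 2.6895/0.06² = 747.1 per side, about 1,494 in total (1,496 if rounded up by side). Power is Φ(0.550) = 70.9% with 600 per side and Φ(0.487) = 68.7% with 570 per side. Taking 24% off the diluted control rate of 24.6% gives 70.1% and 67.8%.

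**5. Other readings of the loss and the factorial margin.**

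| Reading | Observed reduction | Power at 1,200 |
|---|---|---|
| 5%/5% crossover, loss removes patients | 27.4% | 81.6% (79.6% at 1,140) |
| 5%/5%, then 5% missing counted as failure in both arms | 22.6% | 72.6% |
| 5% loss treated as extra drop-out | 25.9% | 76.8% |
| No crossover, 5% missing counted as failure | 24.8% | 81.2% |
| Factorial margin, multiplicative effects, 5%/5% | 27.4% | 73.4% |
| Factorial margin, additive effects, 5%/5% | 32.3% | 86.9% |

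In the second row the rates are 0.05 + 0.95×24.625% = 28.4% and 0.05 + 0.95×17.875% = 22.0%. The fourth row comes nearest to 24% at 80% power, but it leaves out the drop-in and drop-out that the article says are included. No reading tried that keeps the stated inputs gives 24% with 80% power at 1,200.

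**The case against.** The strongest defence is that the figures that fix the design agree with one another: 25%, 30%, 80%, the three allowances of 5%, 932 and 1,200. The target effect is the 30% reduction that the clinicians judged enough to change practice, and the 24% only describes it after dilution. Correcting the figure to 27% changes no patient number, test or procedure. All of this stands, and it limits the severity.

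A reader might go further in three ways that the documents do not support.

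- **That the trial is underpowered at about 70%.** This would follow only if 24% were the planning assumption. The size of 1,200 is reproduced to within about 1% from the other inputs, without the 24%.
- **That 24% shows a 15% drop-in was meant.** The secondary sample size uses "5% loss to follow up, 15% drop-in and 5% drop-out". With those values the primary rates become 23.875% and 17.875%, a 6-point difference. That is 24% of the undiluted 25%, but 25.1% on the base that gives 27.4% above. Applying the squared factor 0.90² = 0.81 to the effect also comes close (0.30×0.81 = 24.3%). The article does not say where 24% came from.
- **That 5% drop-in for one outcome and 15% for the other is a contradiction.** The secondary outcome is assessed at 6 months, after study drug has stopped at 3 months, and other anti-platelet agents are barred only during study medication. More drop-in by then is plausible.

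One objection bears on the correction itself: 27% is not what the stated primary analysis would show if 5% were missing and counted as failures. That is right, and the corrected sentence should say so.

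**Conclusion.** The 24% is wrong as written. The stated 5% drop-in and 5% drop-out give an observed reduction of 27.4%, or 27.0% of the 25% control rate. The 1,200 patients and 80% power agree with that figure and not with 24%, at which power is about 71%, or 69% after 5% loss. The gap is about 10 points of power, or roughly 340 evaluable patients (1,494 against 1,151), so it is not rounding.

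The power of about 70% refers to an observed, already diluted, 24%. A 24% reduction under full compliance, diluted by the same crossover, would be 24.7% versus 19.3%, with about 60 to 62% power (1,140 and 1,200 patients).

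The result assumes the pooled two-proportion formula, which reproduces 932, and loss that removes patients, which brings the size to about 1,200. Severity is minor to moderate: a stated detectable effect is wrong, while the sample size is consistent with the other stated inputs.

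**What to change.** If 5% drop-in and 5% drop-out are the intended assumptions, change 24% to about 27%. Add that this is before patients without an 84-day measure are counted as failures, and that with 5% missing in each arm the observed reduction would be about 23% and power at 1,200 about 73%.

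If 24% is the intended observed effect, restate the non-compliance assumptions that lead to it and give power at 1,200 as about 70%.

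The sponsor must say which applies. The first option is one corrected figure and one added clause, with no effect on recruitment, conduct or analysis. The second also changes only text, but it lowers the power claimed for the primary comparisons.

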### Study Procedures

Participants will be recruited from public and private hospital renal units providing haemodialysis and vascular access services in Australia and New Zealand. Patients will meet the inclusion and exclusion criteria and be scheduled to undergo surgery for creation of a de novo AV fistula. Processes to identify and screen all potential recruits will be established within each centre with consultation with the Trial Management Committee.

Patient consent forms will be approved by the Human Research Ethics Committee at each participating site prior to the beginning of the trial. A sample consent form and patient information sheet is provided to participating sites. Participating sites will file a copy of the approved consent form and information sheet for their site with the coordinating office. After discussing the trial, ample time will be given to the participant, accompanying person or legal representative to inquire about the trial and decide whether to participate. No person involved with the trial will coerce or unduly influence the decision of a patient to participate in a trial. A copy of the signed consent form and the patient information sheet will be supplied to the participant. Patient consent must be obtained prior to the registration or initiation of trial procedures. Patients will not be randomised until a signed consent form is filed at site and notification is received by the coordinating office.

The Trial Management Committee will monitor the medical literature, and any other relevant information impacting on the continuation of the trial. Consent forms and patient information sheets will be revised should any relevant and important new information become available.

Registration will occur when subjects come for their surgical consultation prior to the operation to create the AVF. The patient will have an initial consultation with a study renal physician or surgeon to discuss study participation. This will include a preliminary eligibility check. Consenting patients will be registered by emailing or faxing a completed registration form to the coordinating centre. The registration form also serves as notification of completion of a patient consent form. The patient will also be randomised at this time. Stratification will occur for study site, incident versus prevalent patient status and upper vs. lower arm site. Patients will be randomised to one of four treatment groups in equal proportion.

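### The stated observed relative risk reduction of 24% does not follow from the stated drop-in, drop-out and loss, which give 27.4% or 22.6% depending on how lost patients are handled

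*Protocol article*

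**What the plan says.** All the design inputs are in the protocol article, under the sample size calculation for the primary outcome.

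- Control rate: "The event rate for the primary outcome (failure of primary patency) is estimated to be 25% at three months in the control group".
- Effect: "If a 30% relative risk reduction is achievable with either aspirin or omega-3 fatty acids".
- Size: "with 80% power and a significance level of 5%, 1200 study subjects will be required", with 300 in each of the four cells.
- Non-compliance: "This allows for 5% drop-in from placebo to active treatment (either aspirin or omega-3 fatty acids), 5% drop-out from study treatment". Patients who drop out are taken to revert to placebo risk, and a further 5% are lost to follow-up.
- Diluted effect: "This is equivalent to an observed relative risk reduction of 24" per cent.
- Without the compliance adjustment, the stated size is 932.

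Study Procedures fixes the allocation: "Patients will be randomised to one of four treatment groups in equal proportion". Each drug is therefore compared as 600 against 600.

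The Analysis section specifies a chi-square test for each drug and adds: "Tests of hypotheses will be at the 5% significance level, and 2-sided p-values will be used". It includes every randomised patient in the primary analysis and counts a missing 84-day measure as a failure. A secondary analysis uses only patients who have that measure.

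**The concern.** The 24% is the plan's only statement of the effect that should be visible after non-compliance. Placed directly after the 1,200 and the 80%, it tells the reader that the trial has 80% power for an observed reduction of 24%. Crossover of 5% in each direction should shrink a 30% reduction by roughly one tenth, to about 27%, not by one fifth.

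If the sentence is wrong, a reader who weighs a null result against 24% credits the trial with more sensitivity than it has. If instead 24% is what the investigators expect, the stated crossover rates or the stated power cannot be right.

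**Working it through.** **Formula.** For two proportions with pooled variance, the number per margin is n = [1.96·√(2p̄(1−p̄)) + 0.842·√(p₁(1−p₁) + p₂(1−p₂))]² / (p₁−p₂)². The test is two-sided at 5%, with 80% power and 1:1 margins. The 25% is used as the control rate of the margin, which is what the plan's own 932 implies.

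**Step 1: the plan's unadjusted figure.** With p₁ = 0.25 and p₂ = 0.70 × 0.25 = 0.175, n = 465.8 per margin. The total is 931.7, or 932 in whole patients. This matches the plan and identifies its method as a two-sided comparison.

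**Step 2: apply the stated crossover.**
- Control: 0.95 × 0.25 + 0.05 × 0.175 = 0.24625
- Active: 0.95 × 0.175 + 0.05 × 0.25 = 0.17875
- Observed relative reduction: 1 − 0.17875/0.24625 = 27.4%

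**Step 3: the plan's adjusted figure.** The rates in Step 2 need 1,151 evaluable patients. Dividing by 0.95 for loss gives 1,211, within 1% of 1,200. With 1,200 randomised and 570 analysed per margin, power is 79.6%. The 1,200 and the 80% therefore belong to a 27.4% contrast with lost patients excluded.

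**Step 4: the primary analysis as planned.** Assume that the 5% lost are equal in both groups and all lack the 84-day measure. Counting them as failures gives:
- Control: 0.95 × 0.24625 + 0.05 = 0.2839
- Active: 0.95 × 0.17875 + 0.05 = 0.2198
- Observed relative reduction: 1 − 0.2198/0.2839 = 22.6%
- Power with all 600 per margin: 72.6%

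**Step 5: power if the observed reduction is 24%.**

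| Control rate | Active rate | Power, 570 per margin | Power, 600 per margin |
|---|---|---|---|
| 24.625% | 18.715% | 67.8% | 70.1% |
| 25% | 19% | 68.7% | 70.9% |
| 28.4% (includes missing as failure) | 21.6% | not applicable, all are analysed | 77.9% |

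On the first two rows, 80% power would need about 1,495 to 1,525 evaluable patients, or about 1,575 to 1,605 randomised with 5% loss.

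**The case against.** The strongest reply is that loss to follow-up is not neutral in this trial. Because missing measures count as failures and everyone randomised is analysed, lost patients stay in the denominator and dilute the ratio. On that scale the stated inputs give 22.6%, to which 24% is closer than 27.4% is. This stands, and it has two consequences. Replacing 24% with 27% without a label would describe the secondary analysis of patients with a measure. It would also appear to confirm 80% power for a primary analysis that has about 73% on these assumptions. It does not rescue the 24%, which neither route produces.

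A second reply is that the figures that set the size (25%, 30%, 80%, 932 and 1,200) agree with one another, that effect size and clinical relevance rest on the 30%, and that only safety interim analyses are planned. This also stands, and it limits the point to correcting one statement.

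Three stronger readings are tempting but not supported.

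- **The 1,200 is miscalculated, or the trial needs about 1,600.** The 1,200 follows from the stated inputs under the conventional handling of loss. The larger number applies only if 24% is the true diluted effect and lost patients are excluded.
- **Power is simply 68%.** That needs an observed 24% and 570 analysed per margin. With all 600 it is 70 to 71%, and on the missing-as-failure scale about 78%.
- **The 24% was carried over from the secondary outcome.** The shortcut 0.30 × (1 − 0.15 − 0.05) does equal 24.0% with that section's 15% drop-in and 5% drop-out. A one-sided test at 24% also needs roughly 1,178 to 1,200 evaluable patients, although the plan specifies two-sided tests and its 932 is a two-sided figure. The document does not say where the 24% came from, so no origin should be asserted.

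**Conclusion.** The 24% is wrong as written. From the plan's own 5%, 5% and 5%, the observed reduction is 27.4% among patients with an 84-day measure and 22.6% under the planned primary analysis. The first reproduces about 1,200 at 80% power; the second has about 73% power with 600 per margin. At an observed 24%, power is below 80% on every control rate considered, between about 68% and 78%.

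These results assume a marginal control rate of 25%, as in the plan's 932, full reversion to the other group's risk after crossover, and equal loss in both groups. The 22.6% and 73% also assume that the full 5% are missing at 84 days; fewer missing would move both figures up. The error lies in a reported design figure. It does not by itself show that the number of patients is wrong.

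**What to change.** In the sample size section for the primary outcome, replace 24% with about 27% (24.6% against 17.9%). Label it as the reduction among patients with an 84-day measure and as the basis of the 1,200 and 80%. Add a sentence that, with 5% missing and counted as failures, the same inputs give about 22.6% (28.4% against 22.0%) and about 73% power.

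If 24% is the intended diluted effect, state the crossover rates and the handling of missing measures that lead to it, and restate the power of 1,200 accordingly.

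Either way the cost is one or two sentences and no change in patient numbers. The stated sensitivity of the trial becomes somewhat less favourable.
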